# TREATMENT OF SUBJECTS

## Investigational product/treatment

Intervention:

The intervention is a mindfulness training and consists of a structured standardized online program, which has been provided to clients in the general population (http://www.psychologiemagazine.nl/web/Trainingen/Online-training-mindfulness.htm). Every 3 days the patient receives an email message with a link to a website where they are offered text explanations, video clips, sound tracks with mindfulness exercises, breathing exercises, assignments that need to be filled out, and practice suggestions for the coming few days. The online program is further supported by emails and intermittent text messages on the patient’s cell phone. The online training is currently 8 weeks. It will be extended to 12 weeks followed by reminder emails, sms-messages, and suggestions for continuing practice every 2-4 weeks thereafter until a year after the beginning. The low cost of the online programme (€ 30,-) gives the program the potential of being a cost effective intervention. Patients will not be charged for the online program. They will receive a personal code from Psychologie Magazine to start the online mindfulness training. Adherence to the intervention will be monitored by documenting whether the questions have been filled out.

In addition, all patients will receive usual care just like patients in the control group.

Control:

The control group will receive usual care which consists of regular outpatient visits, lifestyle advice regarding healthy nutrition, smoking cessation, physical activity, and stress reduction, and medical therapy and procedures if indicated.

Justification: See section 7.2

## Use of co-intervention (if applicable)

All patients will receive usual care including lifestyle advice for their structural heart disease.

## Escape medication (if applicable)

Not applicable

# INVESTIGATIONAL MEDICINAL PRODUCT

Not applicable

# METHODS

## Study parameters/endpoints

### Main study parameter/endpoint

It is most likely that the mindfulness training will result in an improved quality of life. In this study we set out to search for an even more ambitious goal, and that is to find effects on physical variables. The 6 minute walk test has been chosen as primary outcome since it is a measure of cardiac and overall physical fitness. We expect that the mindfulness training will improve cardiac and overall physical fitness through the mindful breathing exercises, by encouraging a healthy lifestyle, and by reducing chronic anxiety and stress levels.

Primary outcome will be differences between the active intervention and control groups in the mean improvement at 3 months and 1 year, compared to baseline, of age- and sex expected exercise tolerance.

Exercise tolerance will be measured at baseline, 3 months and 1 year with the 6-minute-walk test (in which the distance is measured that a patient can walk within 6 minutes).

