**Sample size calculation**

To demonstrate an improvement of 5% in the active intervention group vs 1% in the control group in exercise tolerance (expressed in percentage exercise tolerance compared to what can be expected given the patient’s age and sex) would require 99 patients in the control group and 198 in the active intervention group (SD10%, alpha=0.05, power=0.90, ratio experimental to controls=2). Even if only 50% of patients in the experimental group adhere to the training, we would in the as-treated analysis compare three groups of each 99 patients, which would give us a power of 0.80. To account for non-adherence and loss to follow-up a total of 330 patients will be randomized. This number of patients will be sufficient to demonstrate a smaller difference (5% vs 2%) in a repeated measurements analysis with a power of 75-90% (2 follow-up measurements, correlation between follow up measurements=0.70, correlation between baseline & follow-up=0.50).

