## Univariable analysis

Short-term results (3 months) and mid-term results (1 year) will be calculated. Differences in mean improvements between the groups will be calculated for all outcome measures expressed on a continuous scale. Analysis with repeated measurement methods (mixed models) will be performed to account for multiple measurements performed during follow-up and for missing values.

Survival analysis will be performed with a failure being an event as defined according to the composite endpoint.

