## Economic Evaluation

If the 3 months and 1-year results indicate effectiveness of the mindfulness training, we will develop a Markov decision model to calculate long-term effectiveness, costs, and cost-effectiveness of offering mindfulness training to patients with structural heart disease. The comparison strategy will be usual care. We will perform the cost-effectiveness analysis from the health care and societal perspective considering a lifetime timeframe.

The model will consider different classes of heart failure, cardiovascular risk factors, cardiac events, quality of life, and costs. Event rates, risk factor changes, quality-of-life, health resource utilization, and cost data obtained from the clinical study will be integrated in the models. All co-investigators will be asked to review the model assumptions and inputs prior to performing the analysis in order to avoid bias. The economic evaluation will be performed in accordance with the Dutch recommendations for cost effectiveness analyses and we will explore UK and USA recommendations and costs in a sensitivity analysis.

Quality of life will be based on results from the trial where possible and where necessary from systematic reviews and Quality of Life catalogues available on the web. Costs that will be considered include direct medical costs (health-care costs for mind-body program, events, admissions, rehabilitation after an event, nursing home care for long-term disability), patient costs (out-of-pocket expenses for the mind-body program, time and travel costs associated with the program), and productivity losses (friction costs). Health-care costs will be estimated by multiplying health-care resource utilization with the cost per unit of resource. Future costs and life years will be discounted.

With the decision model we will calculate the effectiveness, the costs, the incremental cost-effectiveness ratios, the net health benefit, and the net monetary benefit for a number of willingness-to-pay thresholds. We will perform extensive (probabilistic) sensitivity analysis, threshold analysis, and value of information analysis.

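### The primary outcome names two time points, the sample size covers one comparison at alpha 0.05, and the protocol does not say how the two results are combined

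*Protocol*

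**What the plan says.** Protocol section 7.1.1 sets the primary outcome as the difference between the arms "in the mean improvement at 3 months and 1 year, compared to baseline", on the 6-minute walk test expressed relative to what is expected for age and sex. Section 9.3 says: "Short-term results (3 months) and mid-term results (1 year) will be calculated". It then adds mixed models to handle the repeated follow-ups and missing values, without saying which analysis is the primary test.

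The sample size calculation in section 4 is for a single comparison. Its aim is "To demonstrate an improvement of 5% in the active intervention group vs 1% in the control group in exercise tolerance", with "SD10%, alpha=0.05, power=0.90, ratio experimental to controls=2", and it concludes that this "would require 99 patients in the control group and 198 in the active intervention group". In total 330 patients are to be randomised. The same paragraph ends with a second power statement, for a repeated-measurements analysis of a smaller difference (5% vs 2%): power 75-90%, with a correlation of 0.70 between follow-ups and 0.50 between baseline and follow-up.

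Section 9.6 makes the long-term economic model conditional: "If the 3 months and 1-year results indicate effectiveness of the mindfulness training". Section 9.5 plans no interim analysis.

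**The concern.** Two time points are primary, one alpha is stated and one comparison is sized. The protocol gives no order, no split of alpha and no rule on whether one or both must succeed, and it does not name a single mixed-model contrast as the primary test.

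The rules that fit this text have different error rates and different power, and they can give different verdicts on the same data. This could well matter here: the training runs for 12 weeks and is followed only by reminders every 2 to 4 weeks, so an effect seen at 3 months may have faded by 1 year. A rule that accepts either time point could then declare success, a rule that requires both would probably not, and an average would lie between them. What is at stake is the type I error of the primary claim.

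**Working it through.** **Inputs from the protocol (section 4).** Difference 5 − 1 = 4 points; SD 10; alpha 0.05; power 0.90; allocation 2:1; 99 control and 198 intervention; 330 randomised (110 and 220 at 2:1); correlation 0.70 between follow-ups and 0.50 between baseline and follow-up.

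**Assumptions.** Two-sided tests, equal variances at all visits, SD 10 for the improvement score, the same effect at both visits, normal approximation.

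**1. The plan's own figure.** Control n = (1.960 + 1.282)² × 10² × (1 + 1/2) / 4² = 98.5, rounded up to 99, with 198 in the intervention arm. This is an exact match. SE = 10 × √(1/99 + 1/198) = 1.231; 4/1.231 = 3.25; power = Φ(3.25 − 1.96) = 0.901. A one-sided test would need only 81 controls, so the stated figure is one two-sided comparison.

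**2. Correlation of the two tests.** In units of the variance at one visit:
- Change scores: variance 1 + 1 − 2(0.50) = 1; covariance 0.70 − 0.50 − 0.50 + 1 = 0.70; correlation 0.70.
- Baseline-adjusted: variance 1 − 0.50² = 0.75; covariance 0.70 − 0.25 = 0.45; correlation 0.45/0.75 = 0.60.

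**3. Either time point counts, each at 0.05.** Family-wise error = 1 − P(|Z₁| < 1.96 and |Z₂| < 1.96), bivariate normal.

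| Correlation | Error |
|---|---|
| 0.90 | 7.0% |
| 0.70 | 8.35% |
| 0.60 | 8.75% |
| 0 | 9.75% |

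**4. Both time points must succeed, each at 0.05.** Error is at most 5%. Power for 4 points at both visits:

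| Analysis | Mean z at 99/198 | Power at 99/198 | Power at 110/220 |
|---|---|---|---|
| Unadjusted change, correlation 0.70 | 3.25 | 0.849 | 0.888 |
| Baseline-adjusted, correlation 0.60 | 4/(1.231 × √0.75) = 3.75 | 0.937 | 0.960 |

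**5. Alpha halved (0.025 each).** With unadjusted change scores at 99/198, power is 0.843 for each time point taken singly, and 0.917 for success on at least one.

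**6. One test of the average over both follow-ups, at 0.05.** The variance factor is (1 + 0.70)/2 = 0.85 for change scores and 0.85 − 0.25 = 0.60 with baseline adjustment. Error is 5%.

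| Difference | Power at 99/198 | Power at 110/220 |
|---|---|---|
| 4 points | 0.94 to 0.99 | 0.96 to 0.99 |
| 3 points | 0.75 to 0.88 | 0.80 to 0.91 |

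The 3-point row agrees with the protocol's 75-90% for 5% vs 2%.

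**The case against.** The strongest defence is that one longitudinal analysis is the natural reading. Section 9.3 plans mixed models and section 4 gives power for a repeated-measurements analysis with two follow-ups. The sentence on 3-month and 1-year results promises estimates, not two confirmatory tests, and nothing says that success at either visit is enough, which is the reading that gives 8%. The exact contrast and the handling of alpha are also often left to a statistical analysis plan, which was not available for this review.

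Much of this stands, and it rules out three stronger readings that a reader might infer:

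- *That the trial must have either an inflated error rate or power below 0.90.* It need not. The averaged contrast keeps 5% error with power above 0.90 for 4 points, and so does halving alpha with success on at least one visit (0.917). Requiring both visits falls short of 0.90 with unadjusted change scores but not with baseline adjustment. The protocol does not state which of these two analyses applies to the walk test.
- *That section 9.6 sets a success rule requiring both visits.* It only says when the economic model will be built.
- *That the criterion will be chosen after the data are seen.* The protocol alone cannot show this; it shows only that the protocol does not fix the choice.

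What remains is that the primary outcome and the basis for its sample size are both written in this protocol and do not match: two differences are defined and one is sized. The mixed model is planned but never named as the primary test. A later plan would be choosing among rules with different error rates.

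**Conclusion.** The point holds as a missing decision rule for the primary outcome. As written, the protocol does not assure its stated alpha: the error is about 8% if each time point is tested at 0.05 and either counts, and at most 5% if both are required or one contrast is named. No shortfall in power has been shown, because power for 4 points at 99/198 runs from about 0.85 to 0.99 over the rules and analyses that respect the 5% level (0.84 for a single time point at halved alpha).

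The 8% rests on the correlation of 0.70 and stays between 7.0% and 9.75% for correlations from 0.90 to 0. The power figures rest on SD 10 for the improvement score, equal variances and the same effect at both visits. The change should be made, since it protects the primary claim and costs very little.

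**What to change.** In sections 7.1.1 and 9.3, before data are seen, name one primary test. One suitable choice is the intention-to-treat difference between arms averaged over the 3-month and 1-year walk tests, from the planned mixed model, at two-sided 0.05. State whether the baseline walk test is adjusted for. Report the separate 3-month and 1-year differences as secondary. In section 4, tie each power statement to the test and difference it refers to; in particular, the 75-90% belongs to a 3-point difference, not to the 4 points used for 99/198.

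Naming one of the two time points as primary would also settle the matter. If separate claims at both are wanted, test them in a prespecified fixed sequence, each at 0.05, which keeps the family-wise error at 5%.

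The cost is a sentence or two in each section, with no added patients or visits. The downside of the averaged test is that a benefit present at only one visit is diluted in the primary result, though it would still be reported.

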### Secondary study parameters/endpoints

Key secondary outcome (measured at baseline, 3 months, 1 year):

- quality-of-life (SF36), using the mental- and physical composite outcome scales

Other secondary outcomes (measured at baseline, 3 months, 1 year):

- heart rate, blood pressure, resting respiratory rate (markers of cardiac fitness)
- NTproBNP (a biomarker for heart failure)
- cumulative cortisol in 2 cm of hair taken from the scalp (cumulative measure of stress)
- composite endpoint (all-cause mortality, heart failure, arrythmia, cardiac surgery, percutaneous cardiac intervention, electrical cardioversion)
- psychological well-being (Hospital Anxiety Depression questionnaire)
- preference values (societal EuroQol EQ-5D-5L values, societal SF-6D values obtained from the SF-36, VAS rating scale [Philip Moons version])
- Social support (perceived social support scale 12 Blumenthal PSSS12)
- Medical consumption of health-care use
- health care costs
- related non-health care costs (Tic-P)

### Other study parameters (if applicable)

We will document and adjust for baseline levels of traditional cardiovascular risk factors (blood pressure, smoking, lipids levels, body mass index), pre-existing anxiety and depression at baseline, and social economic status.
In the active intervention group we will monitor adherence to the online mindfulness training through the frequency of logging onto the website. In both active intervention and control group we will monitor participation in other mindfulness-based programs, practice of mindfulness-based exercises, and use of complementary care (through a modified Tic-P questionnaire).

## Randomisation, blinding and treatment allocation

(see flowchart on next page)

All potentially eligible patients are asked to participate in a randomized controlled trial. Written informed consent is obtained for extra data collection alongside usual care and for randomization to one of two healthy lifestyle programs. Patients are explained that mindfulness training is the active intervention and that they will have a 50% chance to be randomized to the active intervention group. The general principle of mindfulness is explained and patients are informed that the training is a web-based online training with exercises that they need to do themselves. Further details about the training and how to access the website and their login will be given after randomization.

Patients will be randomized to either offering online mindfulness training plus usual care (active intervention) vs usual care only (control) (which includes advice about a healthy lifestyle). Patients will be randomly assigned to the active intervention (offering mindfulness training plus usual care) vs control (usual care) in the ratio 2:1 to compensate for non-adherence with the intervention. Randomization will be performed by computer using dedicated software designed for this purpose. Block randomization will be used. The block size will be undisclosed until trial completion.

Patients will not be blinded to the intervention itself since they are actively participating in it. They will, however, be asked to avoid describing their training during follow-up visits to other patients, physicians, and investigators in order to ensure single-blinding. To blind investigators, the treatment allocation will remain undisclosed to the observer assessing outcomes and during data analysis. We will confirm observer blinding by asking the assessor of the exercise tolerance tests which treatment arm he/she thinks the patient has been allocated to.

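### Protocol section 7.2 has patients told of a 50% chance of the active arm, but the trial randomises 2:1, a chance of two in three

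*Protocol*

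**What the plan says.** Section 7.2 (Randomisation, blinding and treatment allocation) opens with what patients hear when they are asked to take part. They learn that mindfulness training is the active intervention and that "they will have a 50% chance to be randomized to the active intervention group". On consent, the same paragraph says: "Written informed consent is obtained for extra data collection alongside usual care and for randomization to one of two healthy lifestyle programs".

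The following paragraph sets the allocation itself. Patients are assigned to the offer of training plus usual care or to usual care "in the ratio 2:1 to compensate for non-adherence with the intervention".

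The sample size calculation in section 4 rests on "SD10%, alpha=0.05, power=0.90, ratio experimental to controls=2" and concludes that the trial "would require 99 patients in the control group and 198 in the active intervention group". It then raises the total: "To account for non-adherence and loss to follow-up a total of 330 patients will be randomized".

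Section 10.2 (Recruitment and consent) gives the order of events: written information by post, a telephone call two weeks later with oral information, written consent at the outpatient visit, baseline measurements, and then randomisation by computer.

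**The concern.** Two adjacent paragraphs of section 7.2 give incompatible allocation probabilities. A 50% chance means 1:1, whereas 2:1 means two in three. Both cannot describe the same randomisation.

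The sentence matters because it describes what patients are told about the procedure they are agreeing to. The chance of each arm is a basic fact about that procedure. A patient deciding whether to join would weigh it against what the active arm asks of them, which by section 10.4 is 12 weeks of online training with assignments followed by reminders for another 40 weeks. The ethics committee would also be approving a document with two different answers to the same question.

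**Working it through.** **Inputs**

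- Chance of the active arm as told to patients: 50% (section 7.2).
- Allocation ratio, active to control: k = 2 (section 7.2, and "ratio experimental to controls=2" in section 4).
- Difference to detect: 5% − 1% = 4 percentage points (section 4).
- SD 10%, alpha 0.05, power 0.90 (section 4). The protocol does not say whether alpha is one- or two-sided, so both were tried.
- Total randomised: 330 (section 4).

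**Step 1. Does the sample size confirm 2:1?**

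For two means by the normal approximation, the number of controls is

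n_control = (1 + 1/k) × (z_alpha + z_beta)² × SD² / difference².

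With two-sided alpha, z_alpha = 1.960 and z_beta = 1.282, so (z_alpha + z_beta)² = 10.507, and SD²/difference² = 100/16 = 6.25.

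| Allocation | Alpha | Calculation | Controls | Active | Total |
|---|---|---|---|---|---|
| 2:1 | two-sided | 1.5 × 10.507 × 6.25 = 98.5 | 99 | 198 | 297 |
| 1:1 | two-sided | 2 × 10.507 × 6.25 = 131.3 | 132 | 132 | 264 |
| 2:1 | one-sided | same formula, one-sided z_alpha | 81 | 162 | 243 |

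The first row matches the protocol exactly, and power at 99 and 198 is 0.901. The protocol's second figure, power of 0.80 for 99 against 99, also reproduces (0.804). The other rows do not give the protocol's numbers. The trial was sized for 2:1 with two-sided alpha.

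**Step 2. The chance of the active arm under 2:1**

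P(active) = k/(k + 1) = 2/3 = 66.7%. The planned arm sizes give the same: 198/297 = 66.7%. P(control) = 1/3 = 33.3%.

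**Step 3. Size of the discrepancy**

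66.7% − 50% = 16.7 percentage points. With 330 patients, 2:1 puts 330 × 2/3 = 220 in the active arm and 110 in control.

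**Step 4. Which statement is out of line?**

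The 2:1 ratio appears as the explicit allocation instruction in section 7.2, with a reason attached (non-adherence), and again in section 4, where the arm sizes and the comparison of three groups of 99 depend on it. The 50% appears once, in the description of what patients are told, and no other statement in the protocol supports 1:1.

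**The case against.** **The patient letter is not available.** Section 10.2 refers to the information letter and consent form as separate attachments. A reader might infer that every participant consents on a false figure. The protocol does not show that; it shows only that its own description of what patients are told is wrong. The letter may give the right chance. This limit stands, and it is why the fix includes a check of the letter.

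**The 50% might be programmed into the randomisation.** A reader might infer that the software could be set up 1:1, giving 165 and 165 in place of 220 and 110. Nothing in the text supports this: the allocation instruction is explicit, justified and consistent with section 4. Nor would such an error reduce power on the protocol's own inputs. With all 330 analysed, intention-to-treat power is 0.953 at 165/165 and 0.929 at 220/110. With 50% adherence, the comparison of adherent patients with controls has power 0.843 either way (82.5 against 165, or 110 against 110). The scenario is no part of this point.

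**The reference to two lifestyle programmes.** A reader might also take the consent wording as false because the control arm is usual care only. But sections 5.1 and 7.2 say that usual care includes lifestyle advice, and patients are told that mindfulness training is the active intervention. The wording is loose but not shown to be wrong.

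**The harm is small.** The error understates the chance of being offered an added training that section 10.4 describes as free of risk, and no endpoint or analysis changes. That is fair and limits the consequence, but the number is still wrong in a passage about what patients are told before consenting.

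**Conclusion.** The point holds as an error in the consent information. The protocol describes telling patients a chance of the active arm that is about 17 percentage points below the one its own allocation gives (50% against 66.7%), and no statement in it reconciles the two. As described, this would reach patients consenting to randomisation in a trial of 330.

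It is not a criticism of the 2:1 ratio. If 2:1 is implemented as written, the validity of the randomised comparison, the sample size and the power are unaffected.

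The conclusion assumes that 2:1 is the intended design, which the exact reproduction of 99 and 198 supports. What the letter and consent form say remains open.

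**What to change.** In section 7.2, replace the statement of a 50% chance with a two in three (about 67%) chance of being offered the online training and a one in three chance of usual care alone. Check that the patient information letter and the oral information given by telephone (section 10.2) say the same, correct them if they do not, and notify the ethics committee.

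The cost is one sentence in the protocol, possibly one in the letter, and the notification. No statistical section needs to change.

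If the sponsor had in fact intended 1:1, the change would be larger: the ratio and its rationale in section 7.2 would have to go, and section 4 would need a new calculation (132 per arm on the stated inputs, before any allowance for loss) and a new argument for the as-treated comparison. Nothing in the protocol points that way.
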